## Abstract

During the COVID-19 outbreak, there was a sharp increase in generalized anxiety
disorder (GAD). Acupuncture therapy has the advantages of accurate clinical
efficacy, safety and reliability, few adverse reactions, and no dependence, and
is gradually becoming one of the emerging therapies for treating GAD. We present
a study protocol for a randomized clinical trial with the aim of exploring the
mechanism of brain plasticity in patients with GAD and evaluate the
effectiveness and reliability of acupuncture treatment. Transcranial magnetic
stimulation (TMS) will be used to assess cortical excitability in GAD patients
and healthy people. Sixty-six GAD patients meeting the inclusion criteria will
be randomly divided into two groups: TA group, (treatment with acupuncture and
basic western medicine treatment) and SA group (sham acupuncture and basic
western medicine treatment). Twenty healthy people will be recruited as the
control group (HC). The parameters that will be evaluated are amplitude of motor
evoked potentials (MEPs), cortical resting period (CSP), resting motor threshold
(RMT), and Hamilton Anxiety Scale (HAMA) score. Secondary results will include
blood analysis of γ-aminobutyric acid (GABA), glutamate (Glu), glutamine (Gln),
serotonin (5-HT), and brain-derived nerve growth factor (BDNF). Outcomes will be
assessed at baseline and after the intervention (week 8). This study protocol is
the first clinical trial designed to detect differences in cerebral cortical
excitability between healthy subjects and patients with GAD, and the comparison
of clinical efficacy and reliability before and after acupuncture intervention
is also one of the main contents of the protocol. We hope to find a suitable
non-pharmacological alternative treatment for patients with GAD.

## Introduction

The long-term aspect and repeated outbreaks of COVID-19 have had a serious impact on
China's economy and life. In general, emotional problems are the most prominent
effects of experiences and feelings in the face of public health emergencies, with
common manifestations of psychological symptoms such as anxiety and panic (1,2). A
clear correlation has been observed between the prevalence of anxiety disorders and
the new coronavirus infection (3). Isolation
measures and other factors contributed to the problem (4). In 2020, approximately 374 million individuals worldwide
were afflicted with anxiety disorders, out of which around 76.2 million cases were
attributed to the epidemic itself. Furthermore, there has been a notable surge of
25.6% in the number of patients suffering from anxiety disorders since the advent of
this pandemic in 2020 (3,5). Generalized anxiety disorder (GAD), as the
most common type of anxiety disorder (6), is
characterized by tension, worry, fear, and autonomic nervous dysfunction (7). It is a chronic disabling disease with a
low rate of complete remission and difficult treatment (8). Persistent mental and physical symptoms not only seriously
interfere with the daily life, study, work, and social interaction of GAD patients,
but also seriously impair their physical and mental health (9).

At present, drug therapy is the preferred treatment for GAD (10). Benzodiazepine anti-anxiety drugs, non-benzodiazepine
anti-anxiety drugs, receptor blockers, selective 5-HT reuptake inhibitors, etc. are
common Western medicine drugs, but the long-term use of such drugs can lead to
dependence, addiction, and increased incidence of drug adverse reactions and drug
resistance, reducing the therapeutic effect (11). Therefore, there is an urgent need for a treatment that is
effective, safe, and easy to promote. As a mature and suitable technique of
traditional Chinese medicine (TCM), acupuncture therapy has gradually become one of
the emerging therapies for GAD.

At the present stage, clinical and, especially, mechanistic studies of acupuncture
intervention are quite limited, and only a few scholars have made preliminary
exploration. Here, we present the protocol of a clinical trial that aims to confirm
the effectiveness and reliability of acupuncture therapy in the treatment of GAD
patients and explore the relevant mechanisms to facilitate the further application
of acupuncture therapy.

## Material and Methods

### Study design

The study will be a randomized, parallel-controlled clinical trial. The main
purpose of the study will be to explore the changes of cortical excitability in
patients with GAD and evaluate the effectiveness and reliability of acupuncture
treatment to GAD. The study will enroll 66 GAD patients who meet the inclusion
criteria, and they will be randomly divided at a 1:1 ratio into the TA group
(treatment with acupuncture) and the SA group (sham acupuncture). In addition,
20 healthy people will be recruited as the control group (HC group). For ethical
reasons, patients from both the TA and SA groups will receive basic western
medicine treatment with paroxetine hydrochloride. We will explore whether there
are cortical excitability changes between GAD patients and the healthy people by
comparing the relevant indicators of transcranial magnetic stimulation (TMS) and
evaluate the efficacy of acupuncture by comparing the relevant indicators before
and after treatment between the TA group and the SA group. The flowchart of this
protocol is shown in Figure 1.

**Figure 1 f01:**
[figure not shown]
Study flow chart, in accordance with the CONSORT guidelines.

### Patients with GAD

#### Inclusion criteria

Diagnosis of GAD according to the CCMD-3 Chinese Classification and
Diagnostic Standards for Mental Disorders formulated by the psychiatric
branch of the Chinese Medical Association and the Fifth Diagnostic and
Statistical Manual of Mental Disorders in the US and having been diagnosed
during COVID-19 and having had a quarantine event; Hamilton Anxiety Scale
(HAMA, 14 items) score ≥14 points and <29 points; Age from 18 to 65 years
old (unrestricted sex, right-handed); No treatments within the past three
weeks, including drug, psychological, or physical treatment such as
transcranial magnetic therapy or other acupuncture treatments; Stable
condition, no self-harming or suicidal behavior; Voluntary participation and
signature of the informed consent prior to inclusion.

#### Exclusion criteria

Patients who do not meet the inclusion criteria; Patients with a previous
history of brain trauma, epilepsy, metal implants, cardiovascular and
cerebrovascular diseases, liver, kidney, and other serious somatic and
organic diseases; Patients with schizophrenia, bipolar disorder, or other
mental disorders or physical diseases that can show symptoms of anxiety;
Anxiety due to past and present self-injury, suicidal plan or behavior,
psychotic symptoms, or alcohol and drug addiction; Poor compliance of
acupuncture treatment or fear of acupuncturists; Left-handed; Women with
pregnancy and lactation.

#### Termination criteria

Serious adverse reactions or events and patient cannot continue with the
treatment; During the course of the study, the subject has serious combined
disease or serious disease of other system and cannot continue with the
treatment; The subject has poor compliance and does not cooperate with the
assigned treatment after repeated explanation by the doctor; The participant
requests to withdraw from the study; The participant takes other therapeutic
drugs independently during the treatment period, which may interfere with
research results; Patients lost to follow-up for various reasons.

### Healthy people

#### Inclusion criteria

Aged between 18 and 65 years; Right-handed, any gender; Physical health and
no physical discomfort in the past month; No central nervous system
stimulation such as repeated transcranial magnetic stimulation (rTMS),
transcranial direct current stimulation (TDCS), or peripheral stimulation
such as acupuncture and percutaneous electrical stimulation; No history of
illicit drug use and excessive alcohol consumption; Signing of the informed
consent form and volunteer participation in the investigation.

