#### Exclusion criteria

People with speech disorders; Hypertension, diabetes mellitus, and major
diseases of the heart, liver, kidney, and other organs; History of dementia,
mental illness, palsy, and other neurological diseases; History of
craniocerebral trauma and surgery; Metal artifacts in the body (including
dentures, pacemakers, neurostimulators, medical pumps, etc.); TMS fear and
other reasons for avoiding TMS stimulation; Women with pregnancy and
lactation.

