### Recruitment

We will recruit patients from the acupuncture department, acupuncture ward,
psychological clinic, insomnia outpatient department and subordinate social
health, general clinic of Bao'an Hospital of Traditional Chinese Medicine in
Shenzhen, with COVID-19 quarantine experience, and who are diagnosed with GAD.
All the participants will participate in a pre-enrollment information session
about the treatment and assessments to ensure subject data retention and
completion of follow-up. A WeChat group will be established for all participants
to communicate with doctors and report adverse events at any time.

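### Quarantine experience is required of every GAD patient but not addressed for healthy controls, so the GAD-versus-healthy comparison may be confounded by it

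*Protocol article*

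**What the plan says.** **Patients.** The inclusion criteria for patients with GAD require a diagnosis "during COVID-19 and having had a quarantine event". The Recruitment section repeats the condition, seeking patients in "Shenzhen, with COVID-19 quarantine experience, and who are diagnosed with GAD".

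**Controls.** The inclusion list for healthy people covers age, handedness, health, prior stimulation, substance use and consent. Its health item reads "Physical health and no physical discomfort in the past month". The exclusion list is detailed and includes, for example, "History of dementia", metal in the body and fear of TMS. Neither list mentions quarantine or COVID-19.

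**The comparison.** Study design says the trial will explore whether there "are cortical excitability changes between GAD patients and the healthy people by" comparing TMS indicators. The Abstract calls the study the "first clinical trial designed to detect differences in cerebral cortical excitability between healthy subjects and patients with GAD". Trial status adds that controls also have blood tests, which implies a serum comparison.

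**Comparability and analysis.** Demographic characteristics compares controls with the 66 patients on age (P=0.168) and sex (P=0.781) only. The baseline items named in Data collection and management do not include quarantine history. Statistical analysis names analysis of variance or a rank sum test and describes no adjustment. Limitations of the study does not mention the difference in entry criteria.

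**The concern.** The GAD-versus-healthy comparison is not randomised, so its meaning depends on how the two groups were selected and what was measured in them. One group is 100% quarantined by criterion; the other has an unknown share. If quarantine affects a TMS or serum marker other than through GAD, and some controls were never quarantined, part of the observed difference belongs to quarantine and would be reported as a feature of GAD.

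The authors treat the pandemic setting as relevant to the disorder. The Introduction says a "clear correlation has been observed between the prevalence of anxiety disorders and the new coronavirus infection", and adds that isolation measures contributed. At stake is the interpretation of the mechanistic aim, not the treatment effect.

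**Working it through.** **1. The plan's own figures.** Sample size gives efficacy rates of 70% and 96%, α = 0.05, β = 0.2 and at least 29 per GAD group. With two-sided α and unpooled variances:

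n = (1.960 + 0.842)² × (0.70 × 0.30 + 0.96 × 0.04) / 0.26² = 28.84, so 29.

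With 10% dropout, 29 / 0.90 = 32.2, so 33. The control group follows from the 1:3 ratio: 58 / 3 = 19.3, about 20. These figures reproduce. None of them sizes the GAD-versus-healthy comparison on a TMS or serum difference.

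**2. What 66 versus 20 can detect** (two-sided 0.05, 80% power, normal approximation).

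- SE = √(1/66 + 1/20) = 0.255 SD
- Detectable difference = (1.960 + 0.842) × 0.255 ≈ 0.72 SD

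**3. The bias.** Let p be the share of controls with a quarantine event and d the direct effect of quarantine on the marker in SD. Patients carry the whole of d and controls carry p × d on average, so

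bias = d − p × d = (1 − p) × d.

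The documents give neither p nor d, so the values below are assumptions.

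| p | d | Bias (SD) | Share of the detectable difference |
|---|---|---|---|
| 1 | any | 0 | 0% |
| any | 0 | 0 | 0% |
| 0.8 | 0.3 | 0.06 | 8% |
| 0.5 | 0.5 | 0.25 | 35% |
| 0.2 | 0.5 | 0.40 | 56% |

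**4. Effect on the test.** Suppose GAD itself has no effect and d = 0.5 SD. The chance of a significant GAD-versus-healthy difference is 50% if no control was quarantined (p = 0), 17% if half were (p = 0.5), and the nominal 5% if all were (p = 1).

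**5. What restriction can recover.** Because every patient was quarantined, adjusting for quarantine amounts to comparing patients with the quarantined controls.

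- p = 0.5 leaves 10 controls: 2.802 × √(1/66 + 1/10) ≈ 0.95 SD detectable
- p = 0.2 leaves 4 controls: 2.802 × √(1/66 + 1/4) ≈ 1.44 SD detectable

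**The case against.** **The imbalance is not shown.** The control criteria do not exclude people who were quarantined, Study setting recruits from the general public, and the Introduction describes repeated outbreaks and isolation measures in China. p could be close to 1. This stands: the confounding is possible and uncontrolled in what is shown, but not demonstrated.

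**A direct effect is not shown.** The Introduction links infection and isolation to anxiety, not to MEP amplitude, CSP, RMT or the serum markers. If quarantine acts on the markers only by causing GAD, it is an upstream cause and not a rival explanation. This also stands, and is why d = 0 belongs in the range.

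**The stronger reading.** A reader might infer that no GAD-versus-healthy difference could be attributed to GAD, or that COVID-19 infection is built into the patient group. The documents support neither. The first needs both a real imbalance and a direct effect. The second mistakes the criterion, which is a quarantine event and not infection; infection history is uncontrolled in both groups. That the month without physical discomfort screens out recently infected controls is only an inference, and such a condition could hardly be mirrored in patients whose disorder includes physical symptoms.

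**It may be recorded elsewhere.** The list of baseline items is introduced as examples, and a condensed article may omit case-report-form items. So it cannot be said that the controls' history goes uncollected. The entry criteria, however, are set out in full for both groups and differ on this point.

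**The comparison is exploratory.** Limitations of the study says so, and the sample size rests on the treatment groups. This lowers the stakes, but the Abstract still puts the comparison forward as a distinguishing feature, with TMS measures among the primary outcomes.

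**Conclusion.** The point holds as a limit on interpretation. Quarantine is an entry condition for patients and is left open for controls; the comparability shown covers age and sex only, and no adjustment is described. The GAD-versus-healthy TMS comparison may therefore be confounded by quarantine experience. The same applies to the serum comparison, which is implied and not stated outright. Uncontrolled infection history is a secondary point.

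The size is unknown. It runs from zero, if all controls were quarantined or quarantine has no direct effect, to just over half of the detectable difference at the most unfavourable assumed values in the bias table. Those values are not bounds drawn from the documents. The randomised comparison of true and sham acupuncture is unaffected, because both arms meet the same criterion.

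**What to change.** 1. Ask the 20 controls, described in Trial status as still being tested, the same quarantine question used for patients. Ask all 86 participants about prior COVID-19 infection and its date. If the visit has passed, the WeChat group set up for participants can be used.
2. Report both items by group beside age and sex.
3. Give a GAD-versus-healthy comparison restricted to quarantined controls, or adjusted for infection history, as a descriptive sensitivity analysis with its confidence interval. It should not serve as a test of whether bias is present, since few controls may remain. Controls who were quarantined and stayed free of mental illness are also a selected group.
4. Unless nearly all controls were quarantined, word the conclusion as a comparison of GAD patients with quarantine experience versus healthy people, not as an effect of GAD itself. Add the difference in entry criteria to Limitations of the study.

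The cost is two short questions that rely on recall, one extra descriptive analysis with a wide interval, and a narrower conclusion. No new recruitment and no change to treatment are needed.

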#### Exclusion criteria

People with speech disorders; Hypertension, diabetes mellitus, and major
diseases of the heart, liver, kidney, and other organs; History of dementia,
mental illness, palsy, and other neurological diseases; History of
craniocerebral trauma and surgery; Metal artifacts in the body (including
dentures, pacemakers, neurostimulators, medical pumps, etc.); TMS fear and
other reasons for avoiding TMS stimulation; Women with pregnancy and
lactation.

#### Termination criteria

Motor cortex area not detected by TMS; Fail to receive the treatment within
the prescribed time due to personal reasons; Poor compliance and no
cooperation with the researcher; Personal withdrawal from the study.

### Study setting

The study team will recruit subjects from the general public through the
Publicity Department of Bao'an Hospital of Traditional Chinese Medicine
affiliated to Guangzhou University of Traditional Chinese Medicine. The
treatment will be conducted in the Acupuncture Branch of that hospital. In
total, 86 people will be recruited for this study, 33 in each treatment group
and 20 in the healthy control group. Patients enrolled in the study will be
required to sign an informed consent form and participate in the study on a
voluntary basis. The timeline for patient enrollment, intervention, and
assessment is shown in Figure 2.

**Figure 2 f02:**
[figure not shown]
Enrollment, interventions, and assessments. The line segments in TA
and SA in the graph indicate the duration of treatment. HC: healthy
control group; TA: treatment with acupuncture group; SA: sham
acupuncture group; SILI: safety index laboratory inspection; HAMA:
Hamilton Anxiety Scale; MEPs: amplitude of motor evoked potentials; CSP:
cortical resting period; RMT: resting motor threshold; 5-HT:
5-hydroxytryptamine; Glu: glutamic acid; Gln: glutamine; GABA:
γ-aminobutyric acid; BDNF: brain-derived neurotrophic factor.

### Recruitment

We will recruit patients from the acupuncture department, acupuncture ward,
psychological clinic, insomnia outpatient department and subordinate social
health, general clinic of Bao'an Hospital of Traditional Chinese Medicine in
Shenzhen, with COVID-19 quarantine experience, and who are diagnosed with GAD.
All the participants will participate in a pre-enrollment information session
about the treatment and assessments to ensure subject data retention and
completion of follow-up. A WeChat group will be established for all participants
to communicate with doctors and report adverse events at any time.

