### Blinding

In this study, the acupuncturists cannot be blinded due to the particularity of
the acupuncture treatment, but the participants and the statisticians will be
blinded. Treatment, testing, and follow-up will be performed independently
without interaction between the groups. At the end of 8 weeks, participants in
the acupuncture and sham acupuncture groups will be asked the following
questions to test for blinding: “Are you confident with this treatment?” “Do you
accept this type of acupuncture?” Participants will choose either “Yes” or “No”
to answer the questions. These data will be analyzed at the end of the study. If
the results are not significant, then it can be concluded that blinding was
reliable. To ensure the consistency of treatment, the treatment and testing will
be completed by the same physician. The collectors of the data, the staff, and
the statisticians will not have access to the assigned tasks.

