### TA group

Before undergoing acupuncture treatment, the patient will be asked to lie in the
flat supine position in a quiet environment. The acupuncturist will sterilize
the skin near the selected acupoints with 0.5% tincture of iodine or 75%
alcohol, then they will choose a one-time use stainless steel needle (25×25 mm,
Huatuo Suzhou, China) and insert it into the skin quickly. Needles will be
inserted in the YINTANG (EX-HN3), BAIHUI (DU20), HEGU (LI4), and TAICHONG (LV3)
points and twirled gently to “Deqi”, which is a therapeutic response to
acupuncture that refers to the sense of qi: the patient feels a heavy and
astringent feeling under the needle, with numbness, swelling, or heavy feeling.
After that, the needle will be retained for 30 min. The specific depth of
acupuncture depends on individual factors. When the needle is removed, the
acupuncturist will press the needle hole with a cotton swab for about 1 min to
prevent bleeding. Acupuncture treatment will be performed once a day, 3 times a
week for 8 weeks.

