### SA group

The environment of the treatment, acupuncture location, and treatment frequency
of the SA group will be consistent with those of the TA group. The acupuncturist
will choose a blunt needle (20×25 mm, Huatuo Suzhou) for the SA group and attach
a translucent tube to the same acupoints as in the TA group. Then, the
acupuncturist will insert a blunt needle into the tube and hold the needle
upright. The patient will feel a mild stabbing sensation, but the needle will
not penetrate their skin.

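### A single WeChat group for all participants is hard to square with blinded participants and arms kept apart during follow-up, and it opens an avoidable route to unblinding

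*Protocol article*

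**What the plan says.** Protocol article, Recruitment: "A WeChat group will be established for all participants", with the stated purpose "to communicate with doctors and report adverse events at any time". The article mentions no division of the chat by arm, private channel, limit on posting or rule against discussing treatment.

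Protocol article, Blinding: the acupuncturists know the allocation, "but the participants and the statisticians will be blinded". Treatment, testing and follow-up are to be run independently, "without interaction between the groups".

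The two arms are described as follows.

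- TA group: a needle goes into the skin and is twirled until Deqi, a sensation of heaviness, numbness or swelling. After that "the needle will be retained for 30 min", and on removal the acupuncturist "will press the needle hole with a cotton swab for about 1 min" to stop bleeding.
- SA group: the acupuncturist attaches "a translucent tube to the same acupoints as in the TA group" and holds a blunt needle upright inside it. The patient feels a slight prick, but the needle will "not penetrate their skin".

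The Safety assessment section lists slight bleeding and redness at the needle site among the reactions to be watched for. The Primary outcomes section names HAMA, rated by psychiatric physicians, together with the single-pulse TMS measures.

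**The concern.** Blinding of the patients is one of the main safeguards of the TA versus SA comparison, because the people giving the treatment cannot be blinded. It holds only while a sham patient has no reason to think that others receive something different. One chat holding both arms, open during treatment and used for reporting reactions, gives patients a place to learn this. A remark about a bleeding point or a question about the tube could be enough for an attentive reader.

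HAMA is at stake. A patient who comes to believe that the needling is sham may expect less and describe symptoms differently from one who is sure it is real. A difference between arms at week 8 could then partly reflect expectation. The feature is stated in the article itself, so this is not a complaint that operational detail has been left out.

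**Working it through.** The point rests on comparing sections. The only arithmetic concerns how many patients a change could still reach.

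1. **Who is in the chat.** Recruitment speaks of one group and of all participants. Study setting gives 33 + 33 + 20 = 86 people, of whom 33 + 33 = 66 have an allocation to conceal. Read plainly, TA, SA and healthy participants share one channel.

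2. **What it is for.** Its purpose is contact with doctors and adverse-event reports at any time. Reporting reactions during the treatment period belongs naturally to follow-up, and follow-up is one of the three activities that the Blinding section says are run with the arms apart. This is where the two sections pull against each other.

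3. **Whether a post could be informative.** Setting the arm descriptions side by side:
   - Skin: penetrated in TA, not penetrated in SA.
   - Device: a translucent tube in SA; none is described for TA.
   - Removal: the needle hole is pressed in TA; SA has no needle hole.
   - Sensation: Deqi is sought in TA; a slight prick is expected in SA. This separates the arms less well, since both groups feel something.
   - Reactions: bleeding points to a penetrating needle. Redness is weaker evidence, because the article does not tie it to one arm.

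   The acupoints are the same in both arms, so patients would be comparing like with like.

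4. **Which outcomes could be affected.** HAMA is rated by physicians but draws on what the patient reports, so it is open to changed expectations. MEP amplitude, CSP, RMT and the five blood markers are instrument or laboratory measures and are less exposed.

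5. **Whether the planned check would show it.** The week-8 questions ask about confidence in the treatment and acceptance of this type of acupuncture. They do not ask which treatment the patient believes was given, so they would not reliably reveal unblinding through the chat.

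6. **How many patients a change could still protect.** Trial status gives recruitment from 2 December 2022 to 25 December 2023, which is 365 + 23 = 388 days. Treatment lasts 8 × 7 = 56 days. Assuming even enrolment of the 66 patients and a prompt start of treatment, those still in treatment when recruitment closed number 66 × 56 / 388 = 9.5, or about 10. With earlier enrolment it would be fewer. If the Trial status sentence that all GAD patients are being treated is taken literally, it would be all 66. The article does not settle this.

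No sample size, power or significance level depends on any of these steps.

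**The case against.** The strongest reply is that the Blinding sentence concerns how procedures are carried out: sessions, tests and visits run separately for each arm. The chat is described as contact between patients and doctors, and nothing says that patients are meant to talk to one another. Separate chats per arm, or restricted posting, may exist in the full protocol, and a condensed article need not give chat settings.

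Part of this stands. The narrow reading is possible, so a reader who infers a flat contradiction goes further than the text allows. It does not dispose of the point, because the sentence names follow-up, the chat is stated to be for everyone, and a message addressed to a doctor in a group chat is ordinarily visible to its members. That visibility is an assumption, though a natural one.

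A second reply is that the harm is conjectural. Patients would have to post procedural detail, others would have to read and interpret it, expectations would have to shift, and ratings would have to follow. This also stands as a limit. A reader might infer that HAMA will be biased towards acupuncture, or that more sham patients will drop out. The article supports neither as a fact. It reports no messages, no allocation guesses and no dropout by arm, and HAMA is rated by physicians rather than completed by patients.

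A third reply is that the missing tube in TA is an inference from silence in a condensed text. That is fair, but skin penetration, needle-hole pressing and possible bleeding distinguish the arms without it.

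**Conclusion.** The point holds as a risk created by a stated design feature. One chat for all participants, with no stated split by arm, sits badly with blinded participants and separated follow-up, and the arms differ enough for ordinary posts to reveal the allocation. Unblinding and a resulting bias in HAMA are plausible. The article shows neither that they occurred nor how large they would be, so no figure can be put on the effect. At most 66 randomised patients are exposed, at staggered times over a recruitment period of about 13 months. The TMS and blood outcomes are less vulnerable.

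The conclusion assumes that posts are visible to other members and that the chat is not divided by arm. If the full protocol already provides separate or private channels, one clarifying sentence resolves the matter. It is worth correcting because the remedy is cheap, but it does not by itself invalidate the comparison.

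**What to change.** Bring the Recruitment and Blinding sections into agreement. Replace the shared group with one-to-one messaging to a study doctor, or with an announcement-only channel in which member posting and the member list are disabled. Take adverse-event reports privately. State the arrangement in one sentence of the protocol.

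For patients already in a shared group, record any messages that describe the procedure or a needle-site reaction, with their dates, and report them alongside the blinding results.

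The change alters no treatment, endpoint, sample size or analysis. Its costs are a change of chat settings, the sentence in the protocol with the notification of changes that the article already foresees, and the modest work of reviewing past messages. Because recruitment is complete, prevention helps only patients still under treatment; for the others, the record of messages is all that can be obtained.
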